### Sample size

We aim to recruit 23–30 general medical practices. As the intention is to have a minimum of 15 practices randomised to the intervention, it was determined that a minimum of 23 practices would be needed to provide sufficient data for the trial and to allow for development of the intervention. The maximum that was considered possible to recruit is 30 practices. Practices will be randomised using a randomisation allocation ratio of 2:1 of intervention versus control. Randomising in preference to the intervention will allow us to iteratively develop the intervention more effectively.

As this is a feasibility study, there is no requirement for a formal power calculation. This study is not intended to be powered to identify a clinically meaningful difference between the intervention groups for the primary outcome measures, rather this study aims to provide robust estimates for the likely recruitment and retention rates and give an indication of the potential variability in the proposed outcome measures, which will in turn be used to inform the power calculation for a future definitive RCT. This is discussed further under statistical analyses.

### Recruitment and consent

#### Recruitment

General practices will be identified through contact details publicly available via practice websites and through contact lists provided by the health boards across Wales. Practices will be invited to participate using a standardised invitation via email addressed to the practice manager, along with information about the study. Practice managers will be asked to consult with their team and indicate their interest in participating in the study by responding to the email. They will also need to advise of their practice’s availability for potential workshop dates.

If no response to the initial email is received, a reminder email will be sent followed by a telephone call. A participant flow diagram can be seen in Fig. 2.

**Fig. 2 Fig2:**
[figure not shown]
Participant flow diagram

Practices that take part in the study will be financially reimbursed for their time; the reimbursement amount was decided upon based on input from local GPs. In addition, participants will receive a copy of the intervention handbook that includes the NG12: Suspected cancer: recognition and referral summary tables, and certificates of attendance. Staff members involved in the design and implementation of a new cancer safety netting plan can consider using this as the basis of a quality improvement project for revalidation and appraisal purposes. Educational accreditation of the workshop will be sought for a future main trial.

We are aware that some challenges in the recruitment lay ahead, but we plan to work with the various research infrastructures in Wales to overcome this. We plan to work closely with the Primary Care Specialty Lead and Primary Care Research Managers within Health and Care Research Wales, and we will establish contacts within regional primary care clusters, with health board staff and with R&D departments in order to maximise potential recruitment opportunities. We will also work closely with the practices that agree to take part in order to support their participation in the study. The recruitment methods will be continually assessed and iteratively developed to determine the most appropriate recruitment strategy for a future definitive RCT.

#### Eligibility to participate

As feasibility is the main objective of this study, all types of general medical practice will be eligible for inclusion. This will aid intervention refinement and allow for a better understanding of what is feasible across a range of practices and also why some practices may not be able to take part.

#### Inclusion

Any general practice in Wales is eligible for inclusion. The target audience for the intervention, based on a ‘whole team approach’, includes all practice staff members. These may include, for example, GPs, nurse practitioners, nurses, health care support workers (HCSWs), practice managers, administrators, receptionists or any other practice staff, clinical and non-clinical. We would aim to include any new forms of primary care organisations such as managed GP practice networks or other general medical practice amalgamations, as well as traditional GP partnerships. However, some of these may be unstable practices with no regular GP staff, and as such, they may be difficult to recruit or find it difficult to participate. Practices participating in other research are also eligible for inclusion; they will be asked to notify us of any cancer-related studies they may be participating in via the baseline questionnaire.

#### Exclusion

There are no exclusion criteria.

#### Consent

Practice managers will be sent more detailed study information in the form of a ‘Research Information Sheet for Practices’ (RISP) and a link to an online baseline practice questionnaire after they have expressed an interest to take part in the study. Participating practice managers will need to indicate that they have read the study information and have agreed with consent statements on the first page of the electronic questionnaire before they can proceed. Prior to the commencement of the ThinkCancer! workshop, Participant Information Sheets (PIS) will be provided by members of the research team and written consent will be obtained from all participating members of staff. This will include consent to use anonymised data recorded on paper or audio-file during workshops and workshop feedback forms. At this time point, participants will also be given the option to provide their contact details should they be happy to be contacted for a telephone interview. Those who indicate that they would like to take part will be contacted at least 2 months after the intervention. Participants from practices randomised to the control arm, who do not take part in a workshop, will also have the opportunity to take part in a telephone interview and will be sent an invitation letter via their practice manager. Response to interview invitations and supplying of contact details will be taken as consent to be contacted and informed consent will be obtained verbally at the time of interview.

*Although we will initially contact practice managers, and they will most likely be the person who completes the questionnaire, this task may be delegated to another member of the practice team with a particular interest in the study.*

#### Pre-trial pilot

A local practice, known to the research team, has agreed to participate in a ThinkCancer! pilot workshop prior to full rollout of the feasibility study. The practice is an urban, large 12,000 patient training practice in a moderately deprived region of North East Wales. Data will not be collected or recorded for trial purposes and feedback from those participating will only be used to refine the intervention prior to its delivery across recruited practices.

### Randomisation and blinding

The general medical practice will be the unit of randomisation. Randomisation will be achieved online, through the remote randomisation centre at the North Wales Organisation for Randomisation Trials in Health (NWORTH) at Bangor University. The randomisation system will use a dynamic adaptive allocation algorithm [45] to achieve randomisation, stratified for health board. ThinkCancer! is an open trial where blinding of participants, researchers and the statistician is not possible due to the nature of the intervention and 2:1 ratio for randomisation.

#### Withdrawal criteria

Practices (and individuals within a practice) will be free to withdraw from the trial at any time, and their right to refuse participation will be respected throughout. We will seek to understand their reasons where possible. In terms of the primary outcome measures, as long as it is possible to collect the data, intention-to-treat analysis will be utilised, whether or not the intervention was received or adhered to.

### Data collection

The feasibility study will be used to rehearse data collection approaches and assess their ease of use. Data will be collected at time-points specific to each item and depending on the type of data. All data collected in this study will be anonymised.

#### Proposed clinical effectiveness outcomes

Data relating to the proposed primary outcomes for the future definitive RCT will be collected at baseline and 6 months after randomisation. Two-week wait referral data and PCI data will be collected directly from participating practices via Case Report Forms containing full instructions on how to extract the data from practice IT systems. We will work with the Practice Manager, CSNC or other delegated individuals to achieve this. It is recognised that this is likely to be too short a follow-up period for meaningful differences to be observed, but the main purpose in this case will be to test the feasibility of collecting the data in this way. Additionally, we will explore the availability of 2WW data at health board level.

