**Methods:**

The ThinkCancer! study is a randomised, multisite feasibility trial, with an embedded process evaluation and feasibility economic analysis. Twenty-three to 30 general practices will be recruited across Wales, randomised in a ratio of 2:1 of intervention versus control who will follow usual care. The workshop will be delivered by a GP educator and will be adapted iteratively throughout the trial period. Baseline practice characteristics will be collected via questionnaire. We will also collect primary care intervals (PCI), 2-week wait (2WW) referral rates, conversion rates and detection rates at baseline and 6 months post-randomisation. Participant feedback, researcher reflections and economic costings will be collected following each workshop. A process evaluation will assess implementation using an adapted Normalisation Measure Development (NoMAD) questionnaire and qualitative interviews. An economic feasibility analysis will inform a future economic evaluation.

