Primary care providers (PCPs) play a vital role in the early diagnosis of cancer [16]. A key diagnostic stage is the Primary care interval (PCI), which is the time from first presentation to a GP with a symptom that could be cancer, to the subsequent referral to a specialist in secondary care [17]. However, with an ever expanding role, PCPs are presented with a plethora of non-specific symptoms, of which only a small proportion are caused by cancer, and many overlap with other diseases [6]. Furthermore, with certain cancers, patients may not present with any alarm symptoms [6, 16] which often results in a delayed cancer diagnosis [2]. In addition, guidelines to expedite early cancer diagnosis are often unclear, with great variation in strategies between different GPs [18].

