### Intervention

The proposed intervention, the ThinkCancer! workshop, has four chief components. The first are two educational sessions, one for all clinical staff (the ‘early diagnosis’ session) and one for non-clinical but patient-facing staff (the ‘cancer aware’ session). The early diagnosis session is delivered as a teaching seminar with learning outcomes focussed on NICE NG12 Suspected Cancer: recognition and referral guidelines [27], hot topics exploring the harder to recognise cancer presentations and consultation-level safety netting. As a proposed aid to support and formalise safety netting, a new tool—the Shared Safety Net Action Plan (SSNAP) [41] will be introduced. The SSNAP tool is a co-produced patient-facing information leaflet that can be used by a clinician to give specific safety netting advice to a patient about when and how they should re-present for further medical assessment [41]. This tool can be used in support of patients who present with ‘low risk, but not no risk’ symptoms or in situations where it would be too soon to trigger an urgent referral or diagnostic investigation. Proposed benefits of the tool include increasing patient empowerment to navigate primary care systems in gaining follow-up appointments, and by keeping copies of the tool within the patient record, better record advice and guidance given. This session will also see the introduction of the ThinkCancer! handbook, which will contain all the resources used in the workshop as well as external resources regarding early diagnosis and safety netting, such as NICE guidance and online learning resources. The cancer aware session is less formal with more convenor-led discussion around cancer red flag symptoms that non-clinical staff may encounter. The secondary aim of this session is to gauge and explore issues and norms around raising concerns within the practice team. The third session (the ‘safety netting session’) involves the two final components of the intervention, the co-production of a bespoke Cancer Safety Netting Plan (CSNP) and appointment of a Cancer Safety Netting Champion (CSNC). This session is attended by a combination of clinical and administrative staff who will be involved in the design and implementation of a new plan. The CSNP will evolve from discussions built on three components, learning from the earlier educational parts of the workshop, evaluation of the current practice safety netting systems reported in the practice questionnaire and the attendee’s personal reflections of cancer diagnosis and safety netting. Following this discussion, a summary document highlighting potential new action points will be sent back to the practice for them to take forward and develop. Success in developing and implementing a new practice plan may be increased by the appointment of a champion to drive change and therefore the appointment of a CSNC is explored during this part of the workshop.

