### Outcome measures

The outcomes that will be reported in this feasibility study are as follows:

Recruitment will be assessed quantitatively by capturing the numbers of practices
▪ Approached▪ Interested in participating▪ Consented▪ Randomised

A description of the excluded practices will be included to help identify potential future eligibility criteria and reasons for non-participation will be sought.

Retention will be assessed quantitatively by the numbers of practices providing both baseline and follow-up data.

Data on individual practice characteristics will be collected to:
▪ Describe the studied sample▪ Identify potential effect modifiers▪ Allow identification of ‘usual practice’

The overarching goal of the ThinkCancer! intervention is to change GPs’ and primary care practices’ behaviours and systems, encouraging them to be more cancer-aware and act sooner on clinical presentations that could be cancer, or more effectively safety net cases where concern exists but criteria for immediate referral are not met. The proposed primary clinical outcomes for the definitive RCT relate to the early referral of suspected cancer. They include the 2-week wait (2WW) referral rate and the PCI. The 2WW referral rate is defined as the crude rate of 2WW referrals multiplied by 100,000 and divided by practice list size [42]. The PCI is defined as the time between the date of first presentation and the date of referral [17].

Secondary clinical outcome measures include the conversion rate and the detection rate. The conversion rate is defined as the ‘proportion of 2WW referrals that are subsequently diagnosed with cancer’ [42] and the detection rate consists of the ‘proportion of new cancer cases treated who were referred through the 2WW route’, [42] also known as the sensitivity [43]. These measures will allow us to further explore potential clinical outcomes.

Although it is unlikely that we will detect a difference in the clinical measures in the feasibility study due to the small sample and short duration of follow-up, we do expect these outcome measures to be affected by the ongoing COVID-19 pandemic. However, the feasibility of using these outcomes will be assessed.

The feasibility of using potential clinical primary outcomes, 2WW referral rate, PCI, conversion rates, and detection rates will be assessed quantitatively by determining:

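### The plan lets the Cancer Safety Netting Champion, a role only the workshop creates, extract outcome data, so extractors may differ between arms, with PCI most exposed

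*Protocol article*

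**What the plan says.** Under *Proposed clinical effectiveness outcomes*, 2WW and PCI data come directly from the practices at baseline and at 6 months, on Case Report Forms that carry extraction instructions. On who fills them in, the section says: "We will work with the Practice Manager, CSNC or other delegated individuals to achieve this". It adds that 2WW data at health board level will be explored; PCI is not mentioned there.

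Under *Intervention*, the third workshop session covers "the co-production of a bespoke Cancer Safety Netting Plan (CSNP) and appointment of a Cancer Safety Netting Champion (CSNC". Appointment is not guaranteed: "therefore the appointment of a CSNC is explored during this part of the workshop". Under *Outcome measures*, the number of practices that nominate a champion is itself an adherence measure.

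The Abstract has practices "randomised in a ratio of 2:1 of intervention versus control who will follow usual care", and *Consent* confirms that control-arm staff do not take part in a workshop. *Randomisation and blinding* states: "ThinkCancer! is an open trial where blinding of participants, researchers and the statistician is not possible".

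PCI is a proposed primary outcome for the definitive trial. *Outcome measures* gives its end points: "The PCI is defined as the time between the date of first presentation and the date of referral". *Background* describes it more fully as "the time from first presentation to a GP with a symptom that could be cancer", up to the referral to a specialist.

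**The concern.** One of the two extractor roles named in the plan is a product of the intervention. It can exist in one arm only, and only after randomisation. If a champion extracts PCI in some intervention practices while someone without workshop exposure does so in control practices, a between-arm difference in PCI mixes any change in care with a change in who read the records.

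This matters more for PCI than for 2WW. A 2WW referral is counted. PCI needs a start date, and that means identifying the consultation at which a possible cancer symptom first appeared. The workshop teaches staff about presentations that are hard to recognise, so it may act on the same judgement. That PCI needs this judgement is an inference from its definition; the article does not say so.

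Three things the study is meant to deliver are exposed: the PCI estimates with confidence intervals intended for designing the definitive trial, the completion rates used to judge whether an outcome is feasible, and the collection procedure itself, which this study rehearses.

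**Working it through.** **The plan's own figure.** The only derivable number is the minimum sample: 15 / (2/3) = 22.5, rounded up to 23, which agrees with *Sample size*. At 2:1 this gives about 15.3 intervention and 7.7 control practices at 23, and 20 and 10 at 30. The point does not depend on these numbers.

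**Sections set side by side.**
- Extractor roles allowed: practice manager, CSNC, or another delegate (*Proposed clinical effectiveness outcomes*).
- Practice manager: exists in both arms, but is expected at the workshop in intervention practices (*Progression criteria*).
- CSNC: may exist in intervention practices after the third session; does not arise in control practices (*Intervention*, *Consent*).
- Rule equalising the extractor across arms or time points: none stated.
- Masking of the extractor: none; the trial is open.
- Second source: *Outcome measures* plans to compare health board and practice data for the candidate outcomes in general, but the data collection section names only 2WW at that level.

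**Change over time.** Nobody can act as champion before the workshop. If baseline data are extracted before it and the champion extracts at 6 months, the extractor may have changed, and only in the intervention arm. It need not have: the baseline extractor could be the person later appointed. The baseline questionnaire must be completed before randomisation (*Practice questionnaires*); no such condition is stated for the baseline outcome form. If the baseline value is unshifted and the 6-month value is shifted in one arm, adjusting for baseline leaves the shift in the estimate.

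**Size, by assumption only.** The article gives no PCI mean, standard deviation or extraction error. Let f be the fraction of intervention practices in which the CSNC extracts, and b the shift in mean PCI in those practices, in days. With no shift elsewhere and practices weighted equally, the bias in the between-arm difference is f × b.
- f = 0.25, b = 1: 0.25 days.
- f = 0.5, b = 3: 1.5 days.
- f = 1, b = 5: 5 days.

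b can also be built up from patients. If the start date moves by 14 days in 10% of patients, b = 0.10 × 14 = 1.4 days; if it moves by 60 days in 30%, b = 0.30 × 60 = 18 days. With f from 0.25 to 1, the bias then runs from 0.25 × 1.4 = 0.35 to 1 × 18 = 18 days. Across both sets of assumptions the range is 0.25 to 18 days. The number of practices does not enter f × b, so recruiting more does not reduce it. The width of the range shows that the inputs decide the answer.

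**The case against.** A reader might infer that PCI is measured by different people in the two arms. The documents do not support that. The wording is permissive, practice managers could extract everywhere, not every intervention practice need have a champion, and nothing stops a practice manager from becoming one. This objection stands, and the point is limited to what the plan allows.

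A reader might also infer a bias in favour of the intervention. That is not supported either. Recognising vague symptoms sooner in the record would date the first presentation earlier and lengthen PCI in the intervention arm, while an extractor invested in the workshop might err the other way.

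There are safeguards. The forms carry full extraction instructions, and *Data management* promises source data validation and random checks. The form is not shown and may define the start date tightly. These measures reduce the problem, but nothing stated about them masks the extractor or gives both arms the same preparation.

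Finally, this is a feasibility study with no hypothesis tests and no power for differences, and it will assess whether each outcome is suitable. So no effectiveness conclusion is at risk. But between-arm estimates with 95% confidence intervals are planned, and testing this way of collecting data is the stated main purpose, so a weakness in the procedure remains relevant.

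**Conclusion.** The concern holds in a limited form. The plan permits an extractor role that exists in one arm only and only after randomisation, for a proposed primary outcome of the definitive trial. PCI is the exposed measure; 2WW is less so, being a count with a possible health board comparison. The documents establish neither the direction nor the size of any bias, and the 0.25 to 18 days above is purely illustrative. The conclusion rests on one inference, that dating the first relevant presentation takes judgement. The consequence is for the PCI estimates, for completion rates that a motivated champion could raise in one arm, and for the procedure carried forward. It is a worthwhile low-cost improvement, not a flaw that invalidates the study.

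**What to change.** In *Proposed clinical effectiveness outcomes*:
- Remove the CSNC as a named extractor.
- Have each practice name, before randomisation, one extractor in a role that exists in both arms.
- Use the same person at baseline and 6 months where possible.
- Require the baseline outcome form before randomisation, as is already done for the baseline questionnaire.
- Record the extractor's role and workshop attendance on the form, so that PCI estimates can be described by extractor.

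This changes one section and the form instructions, adds two fields to the form and needs no extra staff. The cost is flexibility: where the champion is the only willing extractor, completion may fall, and the progression criterion for routine data is 70% of practices.

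The remedy is partial. Practice managers in intervention practices are also expected at the workshop, so a common role does not give equal exposure. Recording attendance makes that difference visible but does not remove it. If resources allow, masked or central re-extraction of a sample of PCI records would measure extractor error for the definitive trial.
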